For piloting we will enroll 20 patients and group them into two that is ten patients in each group. We will intervene one group with vitamin D3 supplement 10,000 IU for five consecutive days. Another group will receive stratified dose of vitamin D3 according to age. That is 20,000IU vitamin D3 in children <6 months, 50,000 IU in children 6-12 months and 100,000 IU in children 13-59 months of age on first day and thereafter 10,000 IU for next 4 days. We will observe any adverse event after the intervention and monitor the serum 25(OH)D level on admission, at discharge (day 5) and after two weeks of discharge as the half life of vitamin D3 is two weeks. To collect blood sample after two weeks of discharge parent/guardian will be requested for follow up visit at hospital with the child at that time. In case of failure to visit the hospital study staff will visit their home for follow up of the child and collection of blood sample for serum 25(OH)D level assay. We will also monitor serum calcium level on day of admission, 2nd day and at discharge for safety monitoring as vitamin Ds primary roll is to control the levels of calcium in the body by constantly adding calcium to or taking calcium from bones. Depending on the adverse event and serum 25 (OH)D and calcium level of this pilot phase, we will decide the final dose for vitamin D3 intervention for the study. We will consider the toxic level of 25(OH)D as 250nmol/L33,34 and the upper limit of the serum calcium would be 2.63 mmol/L for safety monitoring.35 If we find serum 25(OH)D and calcium level on admission above this level we will stop further intervention. After finalization of dose in this study we will assay the 25(OH)D and calcium level on admission and on 5th day or earlier at discharge.

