**Definition of severe pneumonia**

Children aged 3 months to 59 months will be diagnosed as a case of severe pneumonia if they have a history of cough and/or respiratory difficulty plus oxygen saturation < 90% or central cyanosis, or severe respiratory distress (grunting, very severe chest in-drawing), or signs of pneumonia with a general danger sign (inability to breastfeed or drink, lethargy or reduced level of consciousness, convulsions), auscultatory findings of decreased or bronchial breath sounds or signs of pleural effusion or empyema.36

If a child presents with severe malnutrition (children with pitting oedema or Z scores below -3 standard deviations (SD) from the median for weight for height or weight for age or height for age) with any sign of pneumonia (any of the WHO defined signs of pneumonia or severe pneumonia or radiological pneumonia) would be considered as severe pneumonia.37

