**Monitor ionized calcium level instead of total serum calcium:**

We will do blood test for serum ionized calcium instead of total serum calcium for the main phase of the study. In our pilot phase of the study we have found about 50% of our enrolled children with severe pneumonia were severely malnourished. These children may have low albumin level and so may not reflect the actual calcium status of the body through total serum calcium. Moreover ionized calcium gives more accurate picture of calcium in blood comparing to total serum calcium.

In that case as we have considered the upper normal limit of total serum calcium for safety monitoring, in case of ionized calcium the upper limit (normal range: 1.15-1.33 mmol/L)38 will be considered for safety monitoring. So the child having ionized calcium above 1.33mmol/L on admission will be stopped from having further intervention and excluded from the study.

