**Treatment of Severe Pneumonia**

The enrolled children will be admitted to the Respiratory Ward of the Dhaka Hospital and placed on bed. Patency of their airway will be assessed and naso-and/or oropharyngeal suction will be given to those requiring them. Oxygen will be administered to those with an oxygenation saturation of 90% or lesser while breathing in room atmosphere. After the initial collection of a blood sample children will be treated according to pneumonia treatment guidelines of the Dhaka Hospital (Community Acquired Pneumonia in Children, Document No. PR/TG/006/00) added in Annexure 4.

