**Monitoring during hospital stay**

#### During the 5 days of hospital stay data will be recorded 8 hourly including pulse and respiratory rates, axillary temperature, chest auscultatory findings, presence/absence of lower chest wall in drawing, oxygen saturation, and history of cough and feeding (Annexure 3). Resolution of sever pneumonia will be defined as absence of all signs of severe pneumonia, such as lower chest wall in drawing, cyanosis, hypoxia or lethargy, convulsion and inability to feed. Resolution of pneumonia will be considered when there is no fever, tachypnoea (RR less than 40 in children above 1 year and RR less than 50 in children below 1 year) for at least 24 hours and the child can be orally fed.

We will also monitor any adverse events suspected for vitamin D3 during hospital stay. Vitamin D3 at normal doses usually has no side effects. Any sign symptoms of vitamin D toxicity such as vomiting, decreased appetite, irritability, constipation, dehydration, fatigue, muscle weakness39  will be monitored and if recorded will be evaluated for hypercalcaemia. If hypercalcaemia develops we will stop further intervention with vitamin D/placebo. Any deterioration of child’s condition such as septic shock, apnoea (cease of respiration for 10-15 seconds) or cardiac arrest requiring the support of bubble CPAP or mechanical ventilation at any time of the study the child will be transferred to ICU and stop further intervention with vitamin D/placebo. And they will receive the standard hospital care and will be reported to ERC (Ethical Review Committee)/DSMB (data safety and monitoring board) as a case of SAE (serious adverse event). Proportion of such children in the two study groups will be compared during data analysis. We will assess serum “25 (OH)D”andcalcium level on admission. If calcium is above the safety level as mentioned above we will discontinue further intervention and exclude the child from the study.

We will also measure the amount of vitamin D patient received through dietary source (infant formula/milk suji) by calculating the total amount of milk received during hospital stay and there by the amount of vitamin D in International Unit (IU) in that amount of diet.

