**Criteria for Discharge**

- Resolution of pneumonia (defined above)
- No co-morbidities requiring hospitalised treatment
- Can be put on oral antibiotic (after resolution of pneumonia)

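### The respiratory discharge criterion does not require that severe pneumonia has resolved, so as written a child can leave observation before the primary event

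*Protocol*

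**What the plan says.** Protocol, Monitoring during hospital stay, defines two states.

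- Resolution of severe pneumonia, the event behind the primary outcome, is "absence of all signs of severe pneumonia, such as lower chest wall in drawing, cyanosis, hypoxia or lethargy, convulsion and inability to feed".
- The second state is introduced by "Resolution of pneumonia will be considered when there is no fever, tachypnoea". It has respiratory-rate cut-offs of 40 per minute above 1 year and 50 below, a duration of at least 24 hours, and a requirement that the child can feed by mouth.

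Protocol, Criteria for Discharge, lists three conditions. The first is "Resolution of pneumonia (defined above"), which points to the second state and not to the primary event. The second is "No co-morbidities requiring hospitalised treatment". The third is that the child can move to an oral antibiotic, and it is tied to resolution of pneumonia.

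Protocol, Definition of severe pneumonia, gives several routes to entry, including "or severe respiratory distress (grunting, very severe chest in-drawing), or signs of pneumonia with a general danger sign". Protocol, Study Intervention, foresees discharge before the dosing course ends: "we will assay the 25(OH)D and calcium level on admission and on 5th day or earlier at discharge".

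**The concern.** In a time-to-event trial run in hospital, discharge ends the observation that dates the event. The discharge rule should therefore imply that the primary event has occurred, or the protocol should provide another way to time it. Here the rule rests on a definition that omits most of the signs making up the primary event.

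Two things are at stake. The first is ascertainment. A child discharged with a severe sign has no recorded time for the primary outcome, and the secondary duration of that sign is cut off in the same way. The second is safety, because the written rule lets a child go home with a sign that the protocol itself counts as severe.

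A statistical analysis plan could say how to handle such a child but could not recover the missing time. The discharge rule is a clinical procedure fixed in the protocol, so the gap has to be closed there.

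**Working it through.** The plan gives no figure on this point, so the check compares the definitions.

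**1. Overlap between the two definitions.** Resolution of severe pneumonia lists six signs that must be absent: in-drawing, cyanosis, hypoxia, lethargy, convulsion and inability to feed. Resolution of pneumonia requires no fever, no tachypnoea and oral feeding. Only feeding is common to both, and neither definition refers to the other.

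**2. What the wording permits.** Treat the six listed severe signs plus fever and tachypnoea as present or absent. The protocol gives the six as examples, so taking them as the full list is an assumption.

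- Resolution of pneumonia fixes three of the eight (fever, tachypnoea, inability to feed) as absent and leaves five free: 2^5 = 32 combinations.
- The primary event needs the other five absent as well: 1 combination.
- Discharge definition met without the primary event: 32 − 1 = 31 of 32.
- If the oxygen rule under Treatment of Severe Pneumonia is taken to remove hypoxia and cyanosis, three signs remain free: 2^3 = 8 combinations, of which 8 − 1 = 7 lack the primary event.

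These count what the wording allows. They are not frequencies. In practice the relevant signs are mainly residual in-drawing and lethargy.

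**3. Can an eligible child reach this state?** Yes, by either of two routes. Fever and tachypnoea may clear first while in-drawing persists. Or they may never have been present: a history of cough with severe respiratory distress is enough to enter, and the case definition names neither fever nor tachypnoea as a requirement.

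**4. Do the other discharge conditions close the gap?** The co-morbidity condition does not, because a persisting sign of the index pneumonia is not a co-morbidity. The oral-antibiotic condition does not either, because it is tied to the same definition.

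**5. Does the dosing course close it?** No. Discharge before day 5 is foreseen. Also, Sample Size Calculation assumes a control mean of 6 days of severe pneumonia, longer than the five dosing days, so completing the course does not imply the event.

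**6. Can follow-up recover the time?** No. Follow up consists of weekly phone calls asking about new respiratory illness, recorded in weekly categories. It cannot date the clearing of in-drawing or lethargy.

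**The case against.** The strongest reply is that an ordered sequence is the natural reading. Severe pneumonia is a form of pneumonia, the protocol defines resolution of the severe form first, and the four status codes on the in-hospital follow-up form run in the same order. That was probably the intent. It is not written as a rule, however, and if it was intended, writing it down changes nothing the sponsor wants.

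Several practical guards also carry weight:

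- **Oxygen.** "Oxygen will be administered to those with an oxygenation saturation of 90% or lesser while breathing in room atmosphere". This makes discharge of a hypoxic or cyanosed child unlikely.
- **Oral switch.** Judging a child fit for oral treatment is a further clinical step. A clinician may well refuse it in a lethargic child, but the criterion names no signs and refers back to the incomplete definition.
- **Malnutrition.** The pilot found that "about 50% of our enrolled children with severe pneumonia were severely malnourished". If the co-morbidity condition keeps such children in hospital, which is an assumption, the gap bears mainly on the rest.
- **Hospital guideline.** Children are treated under an annexed guideline whose text is not in the copy reviewed. It may contain further discharge conditions.

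The authors also made the durations of fever and tachypnoea secondary outcomes, so they expected these signs to be common. The route is narrow. All of this limits how often the gap would matter, but none of it makes the written rule correct.

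A reader might go further and infer that many children will be lost to the primary outcome, or that the treatment comparison is biased or underpowered. The documents do not support this. They give no frequency, allocation is randomised and double blind, and nothing shows the gap falling unequally on the arms. Censoring at discharge would be a likely consequence, since Data Analysis names Kaplan-Meier and Cox methods, but that section states no censoring rule, so this too is an inference.

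**Conclusion.** The point holds as a minor defect in a stated rule. Followed literally, the discharge criterion can be met before the primary event, chiefly by a child with residual lower chest in-drawing or lethargy, and the protocol then has no means of timing that event.

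No rate can be derived, and the number affected is probably low. The conclusion rests on the protocol text alone and on the assumption that the annexed guideline does not already require the severe signs to be absent at discharge. If it does, the remaining fault is that the protocol's own definition disagrees with the guideline. No between-arm bias or loss of power is shown, and the sample size is unaffected.

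**What to change.** In Monitoring during hospital stay, define resolution of pneumonia as all three of the following:

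1. resolution of severe pneumonia, meaning absence of all severe signs as already defined;
2. no fever and no tachypnoea for at least 24 hours;
3. oral feeding.

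Criteria for Discharge then inherits the change through its reference back, as does the oral-antibiotic condition.

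Derive the primary event time from the 8-hourly sign columns of the in-hospital form, with the status box as a cross-check. Two form changes are optional: making the four status codes mutually exclusive, since the code for continuing pneumonia fits a child before or after the primary event, and adding a cyanosis column, which the grid lacks. They are not essential, because the sign columns already largely allow the event time to be recovered.

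The cost is one clause of text, with no extra patients or tests. A few children who still have severe signs would stay slightly longer, and their time to resolution of pneumonia would lengthen accordingly.

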**Criteria for Discharge**

- Resolution of pneumonia (defined above)
- No co-morbidities requiring hospitalised treatment
- Can be put on oral antibiotic (after resolution of pneumonia)

**Follow up:**

Health worker will follow up the study children on a weekly basis over cell phone up to 6 months after discharge. They will be trained on diagnosis of acute respiratory illness according to IMCI (Integrated Management of Childhood Illness) guideline. They will ask the caregiver/mother for any symptoms of new episode of acute respiratory illness. Study children will be given an ID card to facilitate the follow up at home and revisit to the hospital if any illness develop. Follow up will be recorded in a case record form for 24 weeks (6 months) categorized as no acute respiratory illness, no pneumonia (cough and cold), pneumonia, severe pneumonia and other illness. A new episode of pneumonia will be diagnosed if an episode of pneumonia 14 days after the last day of illness of the previous episode of pneumonia occurs.

**SNP analysis:**

DNA sequence variations occur when a single nucleotide (A, T, C, or G) in the genome sequence is altered. A Single nucleotide polymorphism or SNP is a DNA sequence variation occurring when a single nucleotide - A, T, C, or G - in the genome (or other shared sequence) differs between members of a species (or between paired chromosomes in an individual).Each individual has many single nucleotide polymorphisms that together create a unique DNA pattern for that person. Variations in the DNA sequences of humans can affect how humans develop diseases, respond to pathogens, chemicals, drugs, etc.

Some of the children may have genetic polymorphism and so there may be genetic predisposition to disorders with Vitamin D metabolism.

Therefore we will store a blood sample for SNP analysis in future from the study children. We will only look for common polymorphisms, present in 10-20% of individuals, as the sample size is too small to have power for less common polymorphisms.

**DNA preparation for genome-wide association**

We will store blood sample for future DNA extraction from whole blood collected for genome wide association (GWA) from all cases. One million single nucleotide polymorphisms (SNPs) will be genotyped per individual. The goal will be to test if GWA can be used to identify genetic polymorphisms associated with vitamin D deficiency.

We had a preliminary discussion on it with [name] who is the chief of the division of Infectious Diseases and International Health at University of Virginia, who has expertise in this area of work, is a long-time icddr,b collaborator and is interested in this opportunity. We considered including the SNP analysis at a later date by amendment to the protocol, but decided to include our plan in the original protocol, as it is important we secure consent from the study participants for collecting their blood samples and storing the sample for further analysis. Thus we have made the necessary plans for sample collection and storage. We propose to store the blood sample so that we can use it in future and we are working on finalizing the SNP analysis plan and securing the necessary additional resources. We do believe though that it is important that we collect the necessary samples for this analysis, as these are samples we could not easily collect retrospectively from our study participants. We have not yet included [name] name in our investigators list, but will do so (via protocol amendment) once we have a concrete data analysis plan, an MOU between both institutions and the necessary resources.

## Sample Size Calculation and Outcome (Primary and Secondary) Variable(s)

| Clearly mention your assumptions. List the power and precision desired. Describe the optimal conditions to attain the sample size. Justify the sample size that is deemed sufficient to achieve the specific aims. |
| --- |

From the patients records who were admitted to the Matlab Hospital of icddr,b and calculated duration of severe pneumonia (mean=6 , standard deviation=2.5)10. To calculate sample size corresponding to the hypothesis that the Vitamin D supplement will reduce duration of severe pneumonia we assume the following things:

Mean duration in control group m1=6 days

Standard deviation in control group s1=2.5

Mean in Vitamin D group m2= a sequence of duration up to 5 for example, mean duration in this group is 1 or 2 or 3 or 4 or 5 days.

Standard deviation in Vitamin D group s2 = s1=2.5

Probability of Type-I error alpha= 0.05

Power = 90%

The Mathematical formula is for each group

[figure not shown]

Where
[figure not shown]
 and
[figure not shown]
are standard normal deviate at 5% (alpha) and 10% (beta),
[figure not shown]
 is the common variance in this case this is equal to
[figure not shown]
 and
[figure not shown]
 is the squared difference between duration in both groups. Putting all the values we have

[figure not shown]

With above assumption we calculated as series of sample size and then consider 30% dropout in each case we adjust the calculated sample size. The following table gives the result of the sample size calculation.

| Mean in Duration in control group | Mean duration in Vitamin D group | Effect Size  in percentage | Standard deviation is both group | Initial sample size  in each group | Sample size after adjusting 30% dropout |
| --- | --- | --- | --- | --- | --- |
| 6 | 5 | 16.7 | 2.5 | 108 | 155 |
| 6 | 4 | 33.3 | 2.5 | 28 | 40 |
| 6 | 3 | 50.0 | 2.5 | 13 | 19 |
| 6 | 2 | 66.7 | 2.5 | 8 | 12 |
| 6 | 1 | 83.3 | 2.5 | 6 | 9 |

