## Data Analysis

Data will be entered onto a personal computer (PC) and analysed by the principal investigator using STATA. We will perform the Chi-square test to compare categorical variables, and unpaired t test or ANOVA (Analysis of Variance) to compare quantitative variables. Intention to Treat (ITT) analyses will be done for assessing the impact of vitamin D supplementation on the outcome variable. To compare the median duration of each outcome variables Kaplan-Meier survival function plots will be done. To adjust the treatment effects for potential confounding factors and to evaluate the effect modification Cox proportional hazard regression model will be done. P value will be considered as significant when less than 0.05. Risk ratio (RR) will be estimated to compare the recovery rate in the two groups. Incidence rates of pneumonia will be calculated by dividing the number of new episodes of pneumonia by total time at risk for all children. Hazard ratios with 95% CIs will be obtained with Cox proportional-hazards models to measure time to repeat episodes between treatment groups.

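### The sample-size table reproduces only with an undeclared one-sided 5% test; at two-sided 5% the 6 versus 5 day row has about 83% power at the planned 30% dropout, not 90%

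*Protocol*

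**What the plan says.** The section Sample Size Calculation and Outcome (Primary and Secondary) Variable(s) lists its inputs: "Probability of Type-I error alpha= 0.05", power 90%, "Mean duration in control group m1=6 days", "Standard deviation in Vitamin D group s2 = s1=2.5", and a range of treated-group means ("mean duration in this group is 1 or 2 or 3 or 4 or 5 days"). The formula is an image that cannot be seen here, but the text beneath it says that the two deviates "are standard normal deviate at 5% (alpha) and 10% (beta".

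The section then reports a set of results ("With above assumption we calculated as series of sample size"), each inflated for 30% dropout. The row for the smallest effect reads "6 | 5 | 16.7 | 2.5 | 108 | 155": 108 per group before dropout and 155 after. The other four rows run down to 6 and 9 per group. No row is named as the trial's size. The only fixed number of children elsewhere in the protocol is the 20 for the pilot.

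The Data Analysis section plans chi-square tests, unpaired t tests or ANOVA, and Cox models, with one significance rule: "P value will be considered as significant when less than 0.05". Neither section uses the word one-sided or two-sided.

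**The concern.** A deviate taken at the full 5% belongs to a one-sided test. A rule of P below 0.05, attached to t tests, ANOVA and chi-square tests without further comment, is ordinarily two-sided, and ANOVA and chi-square have no direction at all. If the size was computed one way and the test will be run the other way, the stated 90% power does not belong to the test that will be reported.

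At stake is the power for the primary outcome at the smallest effect considered, a one-day shortening. A reader who takes 90% at face value would read a null result as stronger evidence against a one-day benefit than the design supports.

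**Working it through.** **Inputs.** From the sample-size section: control mean 6 days, treated mean 5 to 1 days (difference d = 1 to 5), common SD s = 2.5, alpha 0.05, power 90%, dropout 30%. From Study Intervention: equal allocation. From Data Analysis: significance at P below 0.05.

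**Step 1: reproduce the printed sizes.** The normal approximation per group is n = 2 s² (z_α + z_β)² / d². For d = 1:

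- one-sided 5%: 12.5 × (1.645 + 1.282)² = 107.05, so 108;
- two-sided 5%: 12.5 × (1.960 + 1.282)² = 131.34, so 132.

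(Products use unrounded deviates.) The exact t-test version takes the smallest n whose noncentral-t power reaches 90%. All rows:

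| d (days) | Printed | One-sided, t | One-sided, normal | Two-sided, t | Two-sided, normal |
| --- | --- | --- | --- | --- | --- |
| 1 | 108 | 108 | 108 | 133 | 132 |
| 2 | 28 | 28 | 27 | 34 | 33 |
| 3 | 13 | 13 | 12 | 16 | 15 |
| 4 | 8 | 8 | 7 | 10 | 9 |
| 5 | 6 | 6 | 5 | 7 | 6 |

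Only the one-sided t test matches all five rows. The two-sided normal formula meets the table at d = 5 alone and misses the other four rows.

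**Step 2: reproduce the dropout column.** Dividing by 0.7 and rounding up: 108/0.7 = 154.3, so 155; 28/0.7 = 40; 13/0.7 = 18.6, so 19; 8/0.7 = 11.4, so 12; 6/0.7 = 8.6, so 9. All five printed values are matched, so the inflation itself is correct.

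**Step 3: power of the 6 versus 5 day row.** With 108 evaluable per group the standardised difference is 1 / (2.5 × √(2/108)) = 2.939.

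- One-sided 5%: 90.2% (normal), 90.1% (t). This is the protocol's 90%.
- Two-sided 5%: Φ(2.939 − 1.960) = 83.6% (normal), 83.3% (t).

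**Step 4: dependence on dropout, two-sided 5%, 155 enrolled per group.**

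- 30% lost, 108 evaluable: 83.3%.
- 90% needs 133 evaluable, so dropout of at most 1 − 133/155 = 14.2%.
- None lost, 155 evaluable: 93.9%.

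**Step 5: size needed to keep 90% at 30% dropout.** 133/0.7 = 190 per group, which is 35 per group more than the printed 155. The full two-sided column is 133, 34, 16, 10, 7 before dropout and 190, 49, 23, 15, 10 after.

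**The case against.** The strongest defence is that the protocol never says two-sided. Its hypothesis is directional, the deviate is openly described as taken at 5%, and a t test can be run one-sided. Read alone, the sample-size section is coherent as a one-sided 5% design with 90% power. This stands to the extent that the 83% is conditional on a two-sided test. It does not remove the point: a directional hypothesis does not declare a one-sided test, no section declares one, and the analysis rule as written is ordinarily two-sided.

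The second defence is that 83% is the low end, since it needs the full 30% loss. The primary outcome is observed during the hospital stay, and the protocol does not say whether the 30% refers to inpatient loss or to loss over the six months of telephone follow-up. This also stands, so the power has to be given as a range. But 30% is the protocol's own planning figure, and at that figure the stated power does not hold.

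Some stronger readings are not supported:

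- A reader might cite the 95% confidence intervals as proof that the primary test is two-sided. The only sentence giving that level concerns time to repeat episodes, a secondary outcome. The case rests on the general 0.05 rule and the tests it is attached to.
- A reader might infer that, with no row chosen, the trial could be declared complete at 9 per group. The rows are effect-size scenarios, and no text permits stopping there. What is true is that no row is named as the target.
- A reader might say that the formula shows 1.645. The image is missing. The one-sided deviate is deduced from the wording and the five matching rows, and the plain normal formula with 1.645 reproduces only the first row.

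**Conclusion.** The point holds in conditional form. The table is a one-sided 5% calculation, while the analysis section as ordinarily read tests at two-sided 5%. Under two-sided 5%, the 6 versus 5 day row has about 83% power at the planned 30% dropout, 90% at dropout of about 14% or less, and about 94% with none. At the planned dropout the shortfall is 6 to 7 percentage points, or 25 evaluable children per group (133 against 108).

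This assumes the protocol's own framework: a comparison of means, SD 2.5 in both groups, a one-day difference and equal groups. It does not show that the trial is underpowered at every plausible dropout. It shows that the stated 90% does not go with the stated significance rule and the stated dropout. The unnamed enrolment target is a separate, smaller gap in the same section.

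**What to change.** 1. State in Data Analysis that the primary comparison is two-sided at 5%. If a one-sided 5% test was in fact intended, the protocol must declare it, because the 90% holds only then.
2. Restate the power for the 6 versus 5 day row with 155 enrolled per group: about 83% at 30% dropout and about 94% with none, with 90% reached at about 14% or less. If 90% at 30% dropout is to remain the stated power, replace the initial sizes by 133, 34, 16, 10, 7 and the inflated sizes by 190, 49, 23, 15, 10.
3. Say which row is the enrolment target and label the others as illustrative scenarios. The 6 versus 5 day row is the natural candidate, but the protocol has to say so.

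Restating the power costs a few lines and a less favourable figure, with no extra children. Keeping 90% at 30% dropout costs 35 more per group, 70 in all, relative to 155 per group.

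### The sample-size table is implicitly sized with a one-sided 5% test; on the conventional two-sided reading of the planned tests, its 90% power is about 83% in the 1-day row

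*Protocol*

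**What the plan says.** The protocol's section on sample size and outcome variables lists its assumptions:

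- Type I error: "Probability of Type-I error alpha= 0.05", with no sidedness given, and power of 90%.
- Control mean: "Mean duration in control group m1=6 days".
- Vitamin D mean: "mean duration in this group is 1 or 2 or 3 or 4 or 5 days", so differences of 5 down to 1 day.
- Spread: "Standard deviation in Vitamin D group s2 = s1=2.5".
- Deviates: the two in the formula "are standard normal deviate at 5% (alpha) and 10% (beta"). The formula itself is an image that is not reproduced in the text at hand.

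The table that follows has five rows. The first reads "6 | 5 | 16.7 | 2.5 | 108 | 155": 108 per group before dropout, and 155 after allowing for 30%. The other rows give 28, 13, 8 and 6 per group before dropout. No row is named as the enrolment target.

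The Data Analysis section plans chi-square tests for categorical variables, an unpaired t test or ANOVA for quantitative ones, and Kaplan-Meier and Cox methods for durations. Its decision rule is "P value will be considered as significant when less than 0.05". For repeat episodes of pneumonia it adds "Hazard ratios with 95% CIs will be obtained with Cox proportional-hazards models". Neither section says one-sided or two-sided.

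**The concern.** A deviate taken at 5% is the one-sided value, 1.645; a two-sided 5% test uses 1.960. If the table rests on the first and the results are judged by the second, the 90% belongs to a test other than the one that will be reported.

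What is at stake is how a null result is read. The protocol itself reports that two earlier trials of vitamin D3 in childhood pneumonia showed no effect during hospitalisation, so a null result is a realistic outcome. With 90% power, a true 1-day benefit is missed 1 time in 10. With 83.3% power it is missed 16.7% of the time, or 1 time in 6.

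**Working it through.** **Inputs.** All come from the sample-size section: SD 2.5 in both groups, differences δ of 1 to 5 days, alpha 0.05, power 90%, dropout 30%. Equal allocation comes from the Study Intervention section.

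**Step 1: reproduce the plan's figures.** The normal formula per group is n = 2·SD²·(z_α + z_β)²/δ². With SD = 2.5, 2·SD² = 12.5. For δ = 1:

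- one-sided 5%: 12.5 × (1.645 + 1.282)² = 107.05, rounded up to 108, as printed;
- two-sided 5%: 12.5 × (1.960 + 1.282)² = 131.3, rounded up to 132;
- two-sided 5% with 80% power: 98.11, rounded up to 99.

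Only the one-sided version gives 108. Size per group across all rows, at 90% power:

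| Difference (days) | Printed | One-sided, normal | One-sided, t test | Two-sided, normal | Two-sided, t test |
| --- | --- | --- | --- | --- | --- |
| 1 | 108 | 108 | 107.73 → 108 | 132 | 133 |
| 2 | 28 | 27 | 27.47 → 28 | 33 | 34 |
| 3 | 13 | 12 | 12.63 → 13 | 15 | 16 |
| 4 | 8 | 7 | 7.48 → 8 | 9 | 10 |
| 5 | 6 | 5 | 5.13 → 6 | 6 | 7 |

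The one-sided t-test calculation matches every row. The two-sided t test matches none, and the two-sided normal formula matches only the last.

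The dropout step is sound. Dividing by 0.70 gives 155, 40, 19, 12 and 9, as printed (for example, 108/0.70 = 154.3, rounded up to 155).

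**Step 2: two-sided power at the tabulated sizes.** For row 1 the standardised difference is 1/2.5 = 0.4 and the non-centrality is 0.4 × √(108/2) = 2.939.

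- One-sided: Φ(2.939 − 1.645) = 90.2% (t test 90.1%).
- Two-sided: Φ(2.939 − 1.960) = 83.6% (t test 83.3%).

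| Evaluable per group | Difference (days) | Stated power | Two-sided power, t test |
| --- | --- | --- | --- |
| 108 | 1 | 90% | 83.3% |
| 28 | 2 | 90% | 83.6% |
| 13 | 3 | 90% | 83.5% |
| 8 | 4 | 90% | 84.5% |
| 6 | 5 | 90% | 87.6% |

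**Step 3: what row 1 does deliver at two-sided 5%.**

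- The t-test requirement for 1 day is 132.31 before rounding. With 108 evaluable, 90% power is reached at √(132.31/108) = 1.11 days.
- With 155 enrolled per group, 133 must remain for 90% power at 1 day. 133/155 = 0.858, so loss can be at most about 14%.
- With no loss at all, 155 per group give about 94% power for 1 day.

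**The case against.** The strongest reply is that no contradiction is proven. The protocol never uses the words one-sided or two-sided. A t test can be run either way, the planned chi-square tests do not concern duration, and the only 95% interval mentioned is for repeat episodes, a secondary outcome. The hypothesis is worded as a reduction. A statistical analysis plan not at hand may settle the sidedness.

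Much of this stands. A reader might infer that every planned analysis is two-sided; the document does not say so, and the two-sided reading is a convention. But an expected direction is not a declared one-sided test, an unqualified 0.05 threshold is ordinarily two-sided, and the ANOVA F test has no direction. A later statement of sidedness would not change the deviate on which this table rests.

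A second reply concerns dropout. The primary outcome is observed in hospital, the analysis is by intention to treat, and Kaplan-Meier and Cox methods can keep children who leave early as censored. Losses from the primary analysis may therefore be well below 30%. This also stands, so it would be too strong to say flatly that the trial lacks 90% power. It does not rescue the table, which attaches 90% to 108 evaluable per group and derives 155 from that number.

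Third, the exact match in all five rows comes from a t-test calculation, whereas the text describes normal deviates; the one-sided normal formula matches only the first row and is one child short in each of the others. The one-sided conclusion does not depend on this, because row 1 is 108 by both one-sided methods and 132 or 133 by the two-sided ones.

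Finally, the powers above are for a t test on mean duration. Power for a Cox analysis of time to resolution was not computed.

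**Conclusion.** The point holds as a mismatch between an implicitly one-sided sizing and an analysis section that conventionally reads as two-sided. On that reading, power at the tabulated evaluable sizes is 83.3% to 83.6% in the first three rows, 84.5% in the fourth and 87.6% in the fifth, against a stated 90%. The figure of about 83% should not be applied to the last two rows.

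This rests on the protocol's own SD and differences, a t test on mean duration, a two-sided 5% level, and the full 30% loss from the primary analysis.

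A reader might infer that enrolment has to rise to the two-sided requirement of 133 evaluable, or 133/0.70 = 190 enrolled, per group. The documents do not support that: no row is named as the target, and 83% for a 1-day difference is a usable design if stated correctly. What is wrong is the power figure attached to the sizes.

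**What to change.** In the sample-size section, state that alpha is two-sided 5%. Keep the tabulated sizes and replace the single 90% with the two-sided power for each row: 83.3%, 83.6%, 83.5%, 84.5% and 87.6%. For the first row, wording such as this would do:

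*With 155 enrolled and 108 evaluable per group, a two-sided 5% t test has 83% power for a difference of 1 day, and 90% power for a difference of 1.1 days.*

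State the same two-sided level in the Data Analysis section, so that the two sections agree.

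The cost is one sentence, one table column and a less favourable stated power. Enrolment and trial conduct do not change.
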